## Abstract

**Introduction:**

Growing up with family violence (FV) is potentially harmful both in a short-term and long-term perspective for the child. Early identification and support are therefore important. The purpose of this project (FRIDa) is to gain a deeper knowledge about the identification of and response to FV in the Swedish Child Health Services (CHS). Further, we would like to better understand how structure and organisation together with nurses’ perceptions may contribute to identification and response within the CHS.

**Methods and analysis:**

In this part of the FRIDa-project, we will use a mixed-method design to explore the pattern of identification of, and response to, FV. Approximately 90 000 CHS medical records over 12 months will be analysed with regression analysis to examine how FV identification and response vary by demographic factors. Furthermore, a qualitative interview study will gain information about the organisational barriers and facilitators and nurses’ professional experiences of working with FV within the CHS. The quantitative and qualitative results will be integrated in an explorative data analysis focusing on variations in the frequencies of posed questions, identification and response to FV supported by interview data.

**Ethics and dissemination:**

The study was approved by the Swedish Ethical Review Authority (Reference number 2025-03516-01). Results will be published with open access in international peer-review journals and communicated to national and regional CHS to contribute to the understanding of the long-term clinical work with FV within CHS. It will also add to the advancement of evidence-based practices for identification of, and response to, FV.

**Trial registration number:**

NCT07158983.

Strengths and limitations of this studyA mixed-methods design integrates quantitative register data and qualitative interview data.The large register dataset of approximately 90 000 child health records provides high statistical power for quantitative analyses.The inclusion of two major child health service providers increases variation in organisational and socioeconomic contexts.The study is conducted within a single Swedish region, which may limit transferability to other regions and countries.Voluntary participation in the interview study may introduce selection bias among participating nurses.

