### Research questions

The specific research questions are:

To what extent are questions about FV posed to mothers and fathers, respectively, in CHS?To what extent is ongoing FV identified among parents that have been asked about it?To what extent have reports of concern been made to social services when FV is identified?To what extent are structural factors (eg, CNI) and organisational conditions (eg, professional education and supervision) associated with nurses’ likelihood of inquiring about FV and responding when FV is identified within CHS?What barriers and facilitators do nurses within CHS perceive when asking about FV?What barriers and facilitators do nurses within CHS perceive in providing support to families affected by identified FV?

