#### Registry-based data from CHS medical records

##### Participants

We will make use of registry data from medical records of children enrolled in the CHS during the period 30 June 2024 to 30 June 2025. Approximately 90 000 children are enrolled in the CHS provided by the two included healthcare providers. The included CHS clinics are based in areas with different socioeconomic characteristics (according to CNI) located in the city, suburbs and surrounding municipalities in the Stockholm region.

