##### Data collection

An electronic questionnaire with questions about organisational characteristics of the included CHS clinics will be distributed via a secure web platform (see online supplemental file 1). The questions cover information on the number of nurses employed, their percentage of full-time employment, years of experience in CHS, number of enrolled children and how many of the nurses that have participated in training about FV. The questionnaire also includes questions on staff turnover in the latest year. It is estimated to take about 15 min to complete the questionnaire. The CNI for each CHS clinic is publicly available and will be retrieved from Region Stockholm.

10.1136/bmjopen-2025-115537.supp1Supplementary data

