##### Data integration

Data from medical records on FV assessment will be linked to corresponding clinic-level variables, including CNI and organisational characteristics, to examine how contextual factors may be associated with assessment practices.

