##### Analysis

Descriptive statistics will be used to calculate the frequency of (1) questions about FV posed to parents, (2) identification of ongoing violence and (3) reports of concern following identification. Differences between mothers and fathers in being asked about violence will be examined using appropriate statistical tests depending on the data distribution. Regression analyses will be conducted to explore associations between questions about violence, CNI and organisational and clinic-level variables. All analyses will be conducted using the statistical software IBM SPSS Statistics for Windows, V.31.0 (IBM).

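### The unrestricted claim of high power from about 90 000 records is not supported for the CNI and organisational associations, whose exposures take one value per clinic

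*Protocol article*

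**What the plan says.** The list of strengths and limitations counts the size of the register data as a strength: about 90 000 "child health records provides high statistical power for quantitative analyses". It attaches no effect size, significance level or number of clinics, and does not limit the statement to particular analyses. The figure is the enrolment of the two care providers: "Approximately 90 000 children are enrolled in the CHS provided by the two included healthcare providers" (Participants).

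Research question 4 asks how far "structural factors (eg, CNI) and organisational conditions (eg, professional education and supervision") are associated with nurses' "likelihood of inquiring about FV and responding when FV is identified within CHS". The sources of these exposures are given under Data collection for the clinic characteristics. For CNI: "The CNI for each CHS clinic is publicly available and will be retrieved from Region Stockholm". For staffing, experience, training and turnover: "An electronic questionnaire with questions about organisational characteristics of the included CHS clinics will be distributed via a secure web platform". Under Data integration, the record data "will be linked to corresponding clinic-level variables, including CNI and organisational characteristics".

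The Analysis section of the quantitative part then says: "Regression analyses will be conducted to explore associations between questions about violence, CNI and organisational and clinic-level variables". It does not state the type of regression, the unit of analysis or the handling of clinics. The Abstract describes the records themselves as the material for the regression. The Discussion again relies on the size of the material, there for the rare outcomes.

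**The concern.** The power of an analysis comes from the units over which the exposure varies. CNI and every item of the manager questionnaire are fixed within a clinic, so ten more children at the same clinic add no new exposure value. They only sharpen the estimate of that clinic's own rate of asking. Once that rate is well estimated, what limits precision is how many clinics there are and how much they differ for reasons unrelated to the exposure.

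The protocol expects clinics to differ. It plans to recruit interviewees from clinics with high and with low rates of asking, and the Introduction says that asking depends on workload, turnover and training.

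Two things are at stake. A reader may take the stated power to cover the CNI and organisational associations, which it does not. And if the record count guided the modelling, differences between clinics could pass as associations with CNI or organisation. The Discussion says that the findings may inform organisational support and training.

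**Working it through.** **The plan's own figure.** The article gives no numeric power, so there is nothing to reproduce. The check is whether the record count can carry the claim for clinic-level exposures.

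**Inputs from the article:** about 90 000 children; one CNI value and one set of organisational values per clinic; routine questions asked in infancy (6–8 weeks for mothers, 3–5 months for fathers); children aged 0–5 years enrolled.

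**Assumptions, not in the article:** number of clinics *k* = 40, 60 or 80, of equal size; ICC for being asked 0.005 to 0.10; equal birth-years, so 90 000/6 = 15 000 children at the routine age in 12 months.

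**Formulas,** with *m* = N/*k* records per clinic:
- Design effect DE = 1 + (*m* − 1) × ICC
- Effective N = N/DE, which stays below *k*/ICC whatever *m* is
- Standard errors from records treated as independent are too small by a factor √DE
- True rejection rate of a nominal 5% test under the null = 2 × [1 − Φ(1.96/√DE)]

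**Example:** *k* = 60, N = 15 000, so *m* = 250, with ICC 0.05. DE = 1 + 249 × 0.05 = 13.45. Effective N = 15 000/13.45 = 1115 (cap 60/0.05 = 1200). √DE = 3.67. Rejection rate = 2 × [1 − Φ(0.534)] = 0.59.

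**Rejection rate under the null for the asking outcome, 15 000 children, clustering ignored:**

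| Clinics | ICC 0.005 | ICC 0.01 | ICC 0.05 | ICC 0.10 |
|---|---|---|---|---|
| 40 | 0.25 | 0.37 | 0.66 | 0.75 |
| 60 | 0.19 | 0.29 | 0.59 | 0.70 |
| 80 | 0.16 | 0.25 | 0.54 | 0.66 |

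A simulation of ordinary logistic regression on a clinic-level covariate with no effect (50 clinics, 15 000 records, 1000 runs per setting) gave 0.36, 0.62 and 0.73 at ICC 0.01, 0.05 and 0.10. An analysis of clinic proportions of the same data gave 0.052, 0.043 and 0.044.

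**Does the record count matter?** At 50 clinics and ICC 0.05, effective N is 940 with 15 000 records and 990 with 90 000. Six times the records add about 5% (990/940 = 1.05).

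**Power.** Take 80% v 75% asked, half the clinics in each group, 50 clinics and 90 000 records. Power is 1.00 if records were independent, and 0.98, 0.47 and 0.27 at ICC 0.01, 0.05 and 0.10.

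**The response outcome.** Its denominator is identified cases, which are rare. Suppose 3% of 15 000 are identified (assumption): 450 cases, or 7.5 per clinic at 60 clinics. With ICC 0.05, DE = 1 + 6.5 × 0.05 = 1.325, √DE = 1.15, and the rejection rate is about 0.09. The inflation is much smaller here.

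**Detectable clinic-level association** (one exposure, correlated with the clinic's rate of asking; 80% power, two-sided 5%): *r* = tanh[2.80/√(*k* − 3)].
- *k* = 40: tanh(0.460) = 0.43
- *k* = 60: tanh(0.371) = 0.35
- *k* = 80: tanh(0.319) = 0.31

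**The case against.** The strongest reply is that the article specifies no faulty model. It says only that regression will be used to explore associations. A condensed article may leave the model form to a fuller plan, and that plan may name a multilevel or cluster-robust analysis. This stands: a reader might infer that clustering will be ignored, but the text neither says so nor rules it out, and the rejection rates above hold only if it is. It does not rescue the power statement. A later mixed model would not turn the record count into the source of information about clinic-level exposures.

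A reader might also infer that the study lacks power for research question 4. That is not shown. At ICC 0.01 or below, power for a five-point difference stayed at about 0.82 to 1.00 in the settings tried (30 to 80 clinics). Nor is the claim wrong for every analysis: mothers and fathers are compared largely within clinics, and there the large count may well give high power.

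A third tempting inference is that associations can be estimated only per clinic because no nurse identifier is listed. The list of extracted variables shows no clinic identifier either, although records are to be linked to clinics, so it is evidently not complete. The full list is available only on request.

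Finally, the study is observational and exploratory, and no sample size was derived from the power statement. That limits the severity but does not make the statement correct.

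**Conclusion.** The concern holds in limited form and should be fixed. The unrestricted power statement is not supported for the CNI and organisational associations in research question 4. Their precision is set mainly by the number of clinics and the ICC, with effective N below about clinics/ICC.

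That the record count overstates the information follows from the article's own description of the exposures, given any positive ICC. The size rests on assumed values. For the asking outcome, a record-level analysis that ignored clinics would reject a true null about 16% to 75% of the time (40 to 80 clinics, 15 000 children, ICC 0.005 to 0.10). A smaller ICC would give less. For the rare response outcome the figure is about 9% under the assumptions shown.

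**What to change.** **Strengths list.** Restrict the high-power statement to within-clinic comparisons such as mothers against fathers. For CNI and the organisational variables, give the number of participating clinics and the association detectable with that number, such as *r* = 0.43, 0.35 or 0.31 for 40, 60 or 80 clinics at 80% power. The manager questionnaire is voluntary, so the organisational variables may rest on fewer clinics than CNI does.

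**Analysis section of the quantitative part.** State that associations with CNI and organisational variables will be estimated by a logistic mixed model with a random clinic intercept, or by GEE clustered on clinic with a small-sample correction. In both, the clinic is the unit of inference. The mixed model can be fitted in the software already named (SPSS GENLINMIXED). If GEE is preferred, confirm first that the correction is available there.

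**Cost.** A few sentences and a different procedure, wider intervals, and a less favourable power statement. By the article's timeline the register analysis runs until November 2026.

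**Optional, not required by this argument:** a fixed effect for care provider, and rewording research question 4 at clinic level.

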## Introduction

Family violence (FV) is a serious global public health concern.^1^ The prevalence of FV varies depending on definition, how, when and where data has been collected.^2 3^ Children may experience FV through direct exposure (eg, physical, psychological or sexual abuse) or by witnessing violence between caregivers or other family members. While these forms of exposure often co-occur, they represent conceptually distinct experiences.^4^ Globally, a large proportion of children are exposed to FV.^2^ In Sweden, self-reported data from adolescents regarding experiences during childhood indicate that 12% and 13% have been subjected to psychological or physical abuse by a caregiver, respectively, and around 10% have witnessed violence between adults in the home.^5^

Short-term and long-term consequences for children experiencing FV have been described concerning physical health, cognitive, emotional and behavioural problems or disorders.^6^ Another identified consequence associated with exposure to FV during childhood is the risk of being a victim or perpetrator of FV in adulthood.^7^ The consequences may be similar whether the child has witnessed violence between adults or has been directly exposed to violence.^8^

Early identification of FV within child health services (CHS) is considered an important strategy for mitigating negative effects for children. In Sweden, CHS is a nurse-led, universal service offered free of charge to all children aged 0–5 years and their parents, reaching almost all families. All parents are offered an individual consultation with a CHS nurse during the child’s first 6 months, providing an important opportunity to ask about exposure to FV. The high coverage and repeated contacts over time make CHS a central arena for identifying FV.^9^

Whether detection of FV should be administered through questions on routine or by indication is not evident. Research so far has failed to demonstrate that routine questions about FV reduce the prevalence of FV.^10^ That may, however, be explained by lack of effective interventions, rather than by the identification process. WHO recommends that services with regular contact with women and children consider routine enquiry about FV, whereas services with less frequent contact may instead use targeted questions based on identified risk factors^11^

Few studies have examined how questions on exposure to violence posed to new fathers in the healthcare settings are working. A few Swedish studies from the CHS context report a lower share of fathers than mothers being asked about violence.^12 13^ To our knowledge, no international studies have investigated how fathers are offered the opportunity to answer questions about their own exposure to violence within a child health or parenting support context.

FV exists in all societies and cultures but there is an increased risk in areas with a higher degree of social vulnerability.^14^ Examining whether parents in areas with different socioeconomic conditions are equally likely to be asked about FV is therefore important. Social vulnerability at a societal level can be measured in several ways. One such measure used within CHS is Care Need Index (CNI), a socioeconomic index used to estimate healthcare needs within an area.^15^ It is based on factors such as single parenthood, unemployment, low educational level and proportion of foreign-born residents in the area. A higher CNI indicates a greater need for support and resources in primary healthcare.

Maintaining routines for asking about violence over time can be difficult, as these practices are often influenced by factors such as workload, staff turnover and access to training. Even routines that are initially well implemented may diminish or become less consistently applied over time.^16^ These organisational factors may also influence healthcare professionals’ confidence in addressing violence, including their preparedness to act when violence is identified. Previous research suggests that a prerequisite for healthcare professionals to ask about exposure to violence is to feel confident about actions and steps to follow if violence is identified.^17^ In Swedish CHS, existing research has focused on the implementation phase of such routines.^12 13 17^ Less is known about how these practices are sustained over time and how nurses experience working with them in everyday clinical practice.

The present study addresses this gap by examining the experiences of CHS nurses who have worked with this approach for several years, providing insights into long-term practice rather than initial adoption. Furthermore, the approach in this study includes asking both mothers and fathers in the same family about their own exposure to violence, which is uncommon in previous research. This perspective is important for understanding how routine questions can support violence prevention and parenting support in a more inclusive way.

To sum up, exposure to FV among children is a severe public health problem that could be reduced by early identification and response in CHS. More research is needed to examine the opportunities of mothers and fathers and parents in different socioeconomic areas to be asked about violence during CHS encounters. There is also a need for increased knowledge of the support CHS nurses require to ask about violence and respond when violence is identified, particularly from a long-term perspective.

## Methods and analysis

### Aim

The aim of this project is to gain a deeper knowledge on how FV is identified and responses to FV within the Swedish CHS. Further, we aim to understand how structure and organisation together with nurses’ perceptions may contribute to identification of and response to FV within the CHS.

### Research questions

The specific research questions are:

To what extent are questions about FV posed to mothers and fathers, respectively, in CHS?To what extent is ongoing FV identified among parents that have been asked about it?To what extent have reports of concern been made to social services when FV is identified?To what extent are structural factors (eg, CNI) and organisational conditions (eg, professional education and supervision) associated with nurses’ likelihood of inquiring about FV and responding when FV is identified within CHS?What barriers and facilitators do nurses within CHS perceive when asking about FV?What barriers and facilitators do nurses within CHS perceive in providing support to families affected by identified FV?

### Design

The study will use a mixed-method design including both quantitative and qualitative approaches. In the quantitative part of the study, data from CHS medical records will be used to identify the frequency of questions posed on routine and based on indication and reports of FV within the CHS. Data from clinical managers are used to map the organisational preconditions of the CHS clinics. The qualitative part of the study consists of interviews with nurses to explore their experiences of identifying and responding to identified FV. The combination of methods will support the understanding of the situation around working with identifying FV within CHS. The study protocol was developed according to the Good Reporting of a Mixed Methods Study (GRAMMS). GRAMMS is used as a checklist to ensure that relevant information is included in the study protocol and it will also be used in the reporting of the results.^18^

### Study setting

The study is set in the Stockholm region in Sweden and involves two of the largest caregivers providing CHS in Stockholm region—Stockholm Health Care Services and Capio. Together they account for about half of the children enrolled at CHS clinics in the region. The Stockholm region comprises about 20% of all children residing in Sweden.

FRIDa is a research project aimed at supporting CHS in identifying and responding to FV through structured routines and staff training.^19^ Based on the FRIDa model, routine questions about FV have been implemented in the CHS in the Stockholm region. For the mother, this usually takes place during an individual visit when the child is 6–8 weeks and for the father at an individual visit when the child is 3–5 months. Three questions are asked, relating to (1) prior exposure to FV for the parent, (2) ongoing exposure to FV for the parent and (3) ongoing exposure to FV for the child. Questions on exposure to violence should also be asked at any time based on indication, whenever there is a suspicion of violence.

### Quantitative part

#### Objectives

The objective of the quantitative part of the study is to examine how questions about FV are asked within CHS in the Stockholm region, and how healthcare professionals respond when violence is identified. A further objective is to examine how these practices are associated with organisational and contextual factors at the CHS clinic level.

#### Data sources

The quantitative part will draw on two complementary data sources:

#### Registry-based data from CHS medical records

##### Participants

We will make use of registry data from medical records of children enrolled in the CHS during the period 30 June 2024 to 30 June 2025. Approximately 90 000 children are enrolled in the CHS provided by the two included healthcare providers. The included CHS clinics are based in areas with different socioeconomic characteristics (according to CNI) located in the city, suburbs and surrounding municipalities in the Stockholm region.

